## Discussion

Observational studies have various inherent limitations. It is important to appraise these in an effort to minimize their effects or, at least to account for them when interpreting results. The most important limitations associated with the ESOSVAL-R study include the following:

1. Selection biases: It is virtually impossible to eliminate all biases from the selection process. First, the people most likely to visit the doctor with the greatest frequency are those who are very old or very sick and there is, thus, a greater possibility that these people will be selected for participation. Clinicians may also tend to select patients who are easier to interview (people with higher educational level), to the detriment of other candidates. In order to reduce the possibility of either of these situations' occurring, this point is specifically stressed to the clinicians during their training sessions. A selection outline, based on the healthcare centers' schedules and patient turns, has also been developed to ensure equitable selection.

2. Information biases when data is missing from the electronic clinical record: Although this problem is ever-present when a study is based on data from real clinical practices, various strategies will be applied to minimize its effect: a) It will be necessary to guarantee that all the participating clinicians are up to date on the topic of osteoporosis, that during medical visits they all respond in a similar fashion and that the quality of the electronic clinical records is as high as possible. To this end a training course will be given to all the clinicians selected for participation. These participants will be required to attend class and to complete further on-line training in the skills and knowledge necessary to manage osteoporosis. b) The electronic clinical records system has been modified to ensure that data is recorded correctly and that the registers are maintained uniformly after the recruits' initial medical visits, and during the follow-up period. These improvements in the electronic medical records system applies to all healthcare centers of the Valencia Health Agency, and not only those participating in this study.

3. Biases due to interventions and maturation: Here the risks are twofold. On the one hand, all the participating clinicians will be receiving specific training to prepare them for the study. On the other, since this is an open study, it may be affected by the doctors' learning curves throughout the process. Because of these two factors, follow-up may be more thorough in the participating patients, and they may receive better care than the population at large. This may translate into differences in the incidence of fractures in the sample cohort and in the general population which, in turn, may lead to underestimating the impact of the risk factors for fracture. Any open study is susceptible to this limitation and it's difficult to handle. However, in the case of the ESOSVAL, the training for healthcare professionals is programmed for the beginning of the study, and we hope that this will minimize the impact of this bias. Furthermore, another study will be designed in conjunction with this one to look at the patients of doctors not participating in the ESOSVAL initiative in an effort to identify possible differences in patient management.

4. Biases associated with misclassification: This bias will occur in either of two cases: when fractures of interest are not identified during the follow-up phase or, alternatively, when fractures that have not occurred during the follow-up period are improperly identified as new ones (identifying as fractures occurring during the follow-up period injuries already existing at the time of recruitment, which should have been classified as previous fractures). To limit this problem, different data sources will be used to properly identify all fractures (ABUCASIS, hospital discharge data, A&E records). Doctors will also be trained to distinguish between already existing and new fractures.

In spite of these limitations, ESOSVAL have several strengths. The study will usher in improvements in the electronic clinical records used throughout the Region and provide training to 800 healthcare professionals and this alone can have a direct impact on the quality of the clinical information registered, and on the attention given to one of today's most prevalent diseases. However, the most innovative fact of ESOSVAL is that it will use routine electronic medical records to follow-up a cohort of 14,500 subjects. Although the potential of these databases for research is obvious, no project like ESOSVAL has been conducted in Spain to date with a design like ours, or a similar number of patients and participating healthcare professionals or length of follow-up. This study will provide insight into the possibilities and limits of the use of these systems for research purposes. Finally, the ESOSVAL study will provide information about the real incidence of osteoporotic fracture in the population of the Region of Valencia (which can be useful for the rest of Spain, where there are no studies of incidence) and about the risk factors for fracture in this context. Ultimately, it will help establish a prediction scale for osteoporotic fracture. Not only will this scale constitute a useful prognostic tool, when further developed with research on cost-utility, it will help establish efficient criteria to identify the level of risk at which treatment should be initiated.

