### Specific objectives

1. To describe baseline characteristics of the cohort under study and the prevalence of risk factors for osteoporosis. This objective will reveal the current prevalence of risk factors for osteoporosis in men and women over 50 years in the Region of Valencia.

2. To evaluate the strength of association between risk factors and the incidence of osteoporotic fracture at five years for the overall population over the age of 50, and for the five-year age-sex subgroups. This objective will also be developed specifically for the risk of hip fracture.

3. To analyze using survival models the time relationship between risk factors and the incidence of osteoporotic fracture and the risk of hip fracture.

4. To identify in patients with osteoporotic and hip fracture factors of poor prognostic for survival.

5. To develop and validate a prediction scale for the risk of osteoporotic fracture at five years, specific to the population of the Region of Valencia, Spain.

6. To evaluate the calibration and the discrimination capacity of the FRAX scale in the population of the Region of Valencia and, if necessary, to recalibrate this scale for its use in the Valencia population.

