### Population and sample

Women and men 50 years of age and over, residing in the Region of Valencia receiving health care in centers where the ABUCASIS electronic clinical record system has been implanted. Exclusion criteria included: 1) Non-residents in the Region of Valencia, due to limitations for long-term follow-up; 2) Individuals with cognitive impairments that in the opinion of the collaborating clinicians constitutes a hindrance to collecting information about the variables used in the study; 3) People eligible for public healthcare but receiving services through private insurance companies, due to the limitations for collecting data; 4) People who are physically unable to attend their usual primary healthcare center; institutionalization is not a criterion for exclusion as long as the patient can go to the healthcare center; 5) People of Asian or African decent, because of differences in prevalence of osteoporosis due to ethnic origin. The cohort will be recruited opportunistically from among the patients who attend the collaborating primary care centers during a 15-week period.

The sample size has been calculated with the stpower Cox utility of the STATA^® ^statistics package, under the following assumptions: Alpha error (0.05), power (0.80), standard deviation for the densitometry T-score (0.75), square of the multiple correlation among co-variables (0.10), losses to follow-up of 10%, accumulated incidence of hip fracture of 15‰ after five years of follow-up and a capacity to identify as significant hazard ratios of 33% (change in the frequency of an event associated with a unit of change in the co-variable). These calculations results in a sample size of 14,122 individuals over the age of 50 in whom 180 hip fractures are expected to occur at five years of follow-up. The sample will be distributed according to the age and sex structure of the population over the age of 50 in the Region of Valencia and will be assigned in groups of 36 cases among the approximately 400 participating "practices" (two collaborating health care professionals, typically with one doctor and one nurse, per "practice") in order to be able to build a sample that is faithful to the structure of the population of the Region.

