#### Selection of patients

Patients will be recruited through the participating primary healthcare centers over a 18-week period. The clinicians will select 36 patients opportunistically as they attend the medical practices, distributing them for every day of the week and according to the healthcare centers different schedules. The minimum recommended recruitment frequency is two patients per week, for the 18-week period until reaching 36 recruits with the profile (age and sex) that has been assigned to each participating clinician by the research group.

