### Statistical analysis

Once the recruiting process has been completed, the cohort baseline data will be analyzed. A description will be made of the patients' characteristics along with their current risk factors. The analysis will be stratified by five-year age-sex subgroups. The appropriate parameters (means, proportions) will be used with each variable with their corresponding 95% confidence intervals (CI95%). A bi-variable analysis will also be made to evaluate the relationships between risk factors that are of most interest. Simple Odds Ratios (OR) will be applied to estimate the strength of association and, when necessary, multiple logistic regression models will be used.

At two and five years of follow-up, an analysis will be made of the strength of association between the risk factors and the incidence of osteoporotic fracture in all locations and in the hip. For this, bi-variable analysis and Cox' proportional hazards models will be used. Additionally, a specific model will be developed to analyze the probability of death once a fracture has occurred (controlling for the effect of the different types of fractures).

Next, the most parsimonious of Cox' proportional hazards models will be applied to two-thirds of the sample (approximately 10,000 subjects randomly selected) to develop a scale to predict the risk of osteoporotic fracture. The scale's prediction capacity will be evaluated with the C statistic, and its calibration will be evaluated with the Hosmer-Lemeshow test, or a similar test. The predictive weights of the risk factors obtained in this model will be applied to the remaining third of the database (approximately 5,000 subjects) to evaluate whether prediction capacity (C statistic > 0.75) and calibration (non-significant Hosmer-Lemeshow test) are maintained. Scaling techniques will then be applied to construct a simplified scale on the basis of the validated model.

Finally, the calibration and the capacity for discrimination of the FRAX scale will be evaluated in the population of the Region of Valencia, Spain. If necessary, the FRAX will be recalibrated to make it more appropriate for the population in question. This time, the weights of the original scale will be used in conjunction with the incidence of osteoporotic fracture derived from our study. If the scale shows poor prediction capacity (statistics < 0,75), or if it is not correctly calibrated, it will be recalibrated with the weights derived from our own scale.

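### The selection outline spreads recruits over sessions, not over persons, so objective 1 should claim risk-factor prevalence among primary-care attenders rather than in the Region

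*Protocol article*

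**What the plan says.** Recruitment is opportunistic among people who come to the collaborating centres (Methods/Design, Population and sample). Under Selection of patients: "The clinicians will select 36 patients opportunistically as they attend the medical practices". Recruits are spread over weekdays and centre timetables, within an age and sex profile set by the research group.

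Item 1 of the Discussion (Selection biases) says it is close to impossible to remove all such bias. It then names the first source: "the people most likely to visit the doctor with the greatest frequency are those who are very old or very sick". Two measures follow. The point is stressed in clinician training, and an outline based on the centres' schedules "and patient turns, has also been developed to ensure equitable selection".

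Objective 1 (Specific objectives) carries no such reservation: "This objective will reveal the current prevalence of risk factors for osteoporosis in men and women over 50 years in the Region of Valencia". The Statistical analysis section stratifies the baseline description by five-year age-sex group and says: "The appropriate parameters (means, proportions) will be used with each variable with their corresponding 95% confidence intervals (CI95"%). It does not mention visit frequency.

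**The concern.** The measure offered does not match the bias named. Spreading recruits evenly over sessions makes appointment slots comparable. Someone who fills more slots still has more chances of being picked, and someone with no visit in the recruitment window has none. Training can discourage deliberate picking, but it does not change how often people attend.

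The quotas and strata deal with the very old. They do not deal with the very sick within an age-sex cell. Several listed risk factors plausibly bring people to the doctor, for example oral glucocorticoids, rheumatoid arthritis and osteoporosis treatment. For these, the plan would produce a figure weighted towards frequent attenders and label it as prevalence in the Region's population over 50.

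**Working it through.** **The plan's own figure.** The article gives no precision target for prevalence. Its only sample-size figure comes from the Cox calculation, and it reproduces with a hazard ratio of 1.33 and a two-sided 0.05 test:

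- Events: E = (1.960 + 0.842)² / [0.75² × (ln 1.33)² × (1 − 0.10)] = 190.6.
- Sample size: 190.6 / 0.015 = 12,709; divided by 0.90 this is 14,121, against 14,122 stated.

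This calculation does not bear on prevalence. The cohort size used below is the 14,500 in the Abstract.

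**Inputs for the check**

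- n = 14,500 pooled.
- About 1,036 per stratum, from 14,500 / 14. Fourteen equal strata (seven age bands by two sexes) is an assumption.
- r, the ratio of visit rates between carriers and non-carriers of a factor at the same age and sex. The documents do not give it; 1 to 2 is assumed.

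**Is selection roughly proportional to visits?** Take Poisson visits over 18 weeks and a per-visit selection probability s. The chance of inclusion is 1 − exp(−v × 18/52 × s), with v visits a year. Going from v = 6 to v = 12 multiplies inclusion by 1.98, 1.94 and 1.81 at s = 0.01, 0.03 and 0.1. Proportionality is a fair approximation. The article gives the window as 15 weeks in one place and 18 in another; the conclusion is the same for either.

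**Expected prevalence in the sample.** With true prevalence P, it is rP / (rP + 1 − P). For P = 10% and r = 1.25: 0.125 / (0.125 + 0.90) = 12.2%.

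**Half-width at 10%.** Pooled: 1.96 × √(0.09 / 14,500) = 0.49 points. Stratum: 1.96 × √(0.09 / 1,036) = 1.83 points.

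| r (assumed) | Seen, if truth is 10% | Bias, points | In pooled half-widths | In stratum half-widths |
|---|---|---|---|---|
| 1 | 10.0% | 0 | 0 | 0 |
| 1.25 | 12.2% | 2.2 | 4.5 | 1.2 |
| 1.5 | 14.3% | 4.3 | 8.8 | 2.3 |
| 2 | 18.2% | 8.2 | 16.8 | 4.5 |

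**How large must r be to matter?** For the pooled estimate, r of about 1.08 (true prevalence 5%) or 1.04 (20%) already puts the truth at the edge of the 95% interval. In a stratum of about 1,036 the corresponding ratios are about 1.32 and 1.17. At r = 1.25, coverage in such a stratum is about 65%, 42%, 18% and 9% for true prevalences of 5%, 10%, 20% and 30%. These coverage figures use the interval centred on the biased estimate.

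**The case against.** The strongest reply is that the authors disclose this bias themselves, place it first, and describe their measures as reducing it. That stands. The fault is narrower: the Discussion says the outline secures equity when it cannot, and objective 1 is worded without the reservation.

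Other parts of the reply also stand:

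- A reader might infer that the analysis is fixed as unweighted. The article does not say so. It is silent on weights, and a journal article may leave them to the full plan. The outline's detailed rules are not shown either, only its basis.
- A reader might infer that the intervals are too narrow and will miss the truth. The documents do not show this. Any fault would lie in where the interval is centred, not in its width. Within strata, which is the planned analysis, a modest ratio and a rare factor can still leave fair coverage.
- A reader might infer that every factor is over-represented. Factors unrelated to attendance (r = 1) show no bias. The exclusions of people physically unable to attend and of some with cognitive impairment may lower the observed frequency of fall risk, immobilisation or previous fracture. The admitted tendency to choose patients who are easier to interview could also pull some figures another way.

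None of this makes the outline a remedy for visit frequency or makes attenders the same as the Region's population.

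**Conclusion.** The point holds in limited form. As described, the outline cannot do what the Discussion says it does, and objective 1 claims more than an attender-based sample supports. The direction is likely upward for factors tied to illness or treatment, but it is not established for every factor. The table's sizes rest wholly on assumed visit-rate ratios. What the arithmetic does show is that, at this sample size, even small differences in attendance matter for pooled figures, while in strata the effect depends on the ratio and the prevalence.

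A reader might extend this to the prediction scale. The documents do not support that step: associations and the scale are less directly affected than prevalence, and the main objective does not rest on objective 1. This should be corrected, but it does not call for a redesign.

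**What to change.** 1. In Specific objectives, restate objective 1 as the prevalence of risk factors among men and women over 50 who attend primary care in the Region.
2. In item 1 of the Discussion, replace the claim of equitable selection. Say that the outline balances days and sessions but does not remove over-selection of frequent attenders.
3. If ABUCASIS logs attendances (assumed), add a sensitivity analysis of the objective 1 prevalences. Weight by the inverse of each participant's visits in the prior 12 months, counting the recruitment visit so that no weight is undefined. Use robust standard errors and report the results beside the unweighted cohort figures.

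The weighted analysis should stay a sensitivity analysis. It cannot recover people who never attended, and it assumes that the choice among slots was random.

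The first two changes cost only a narrower claim. The third needs one extra variable and gives somewhat wider intervals. If the design effect were 1.4 to 2.3 (assumed), the pooled half-width at 10% would go from 0.49 to between 0.49 × √1.4 = 0.58 and 0.49 × √2.3 = 0.74 points.

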## Abbreviations

BMD: bone mineral density; DXA: dual energy x-ray absorptiometry; CRF: clinical risk factors; OR: odds ratio.
